## Patient and public involvement

Patients and their caregivers were not involved in the design of the study. During recruitment, all caregivers of children admitted to hospital were given information about the study; those whose children had severe acute malnutrition were approached to give written informed consent. A meeting to disseminate results of the study to participants and their caregivers will be held at the end of the study. An interactive game to engage caregivers in the science underlying malnutrition is being developed in collaboration with experts from the Centre of the Cell, a unique science education centre based at Queen Mary University of London (https://www.centreofthecell.org/).

## Safety reporting

For all adverse events, the study team will assess expectedness and relatedness to study activities. Since this is an observational study without interventions, we anticipate that the risk is minimal; however, serious adverse events will be reported to local ethical review boards (Medical Research Council of Zimbabwe, and University of Zambia Biomedical Research Ethics Committee) and the study sponsor (Queen Mary University of London) according to their respective guidelines.

## Data collection and monitoring

Clinical and demographic data are recorded on paper case report forms. All data are checked for completeness and plausibility before data entry and problems flagged for resolution by the clinical team. All data are double-entered onto a dedicated password-protected online study database and any discrepancies resolved. Study participants are identified on electronic databases only by study numbers (assigned at enrolment); no personal identifiers are entered.

## Ethics and dissemination

The study complies with the principles of the Declaration of Helsinki (2008) and is conducted in compliance with the principles of Good Clinical Practice and local regulatory requirements in each country. Ethical approval was obtained from the University of Zambia Biomedical Research Ethics Committee, the Joint Research Ethics Committee of the University of Zimbabwe and the Medical Research Council of Zimbabwe. The ethical review board of the Sponsor, Queen Mary University of London, provided an advisory review of the study. Since this is an observational study, there is no Data and Safety Monitoring Board.

Results will be disseminated through conference abstracts and peer-reviewed publications and discussed with relevant policymakers and programmers. Study findings will be disseminated to families of participants at face-to-face meetings.

## Time frame and study status

“Enrolment into the SAM cohorts began in July 2016 and ended in March 2018. Enrolment of well-nourished controls is expected to end in March 2019. All participants with SAM will be followed for 48 weeks, with an expected study completion date of March 2019.”

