## Study design

HOPE-SAM is a longitudinal observational cohort study, enrolling between 600–800 children aged 0–59 months admitted with complicated SAM to the tertiary paediatric wards at two sites in Zimbabwe (Parirenyatwa Hospital and Harare Children’s Hospital) and one in Zambia (University Teaching Hospital, Lusaka). Both HIV-positive and HIV-negative children will be enrolled. Throughout this paper, ‘SAM’ refers to all children, regardless of HIV status; where analyses specifically compare children by HIV status, groups are identified as HIV-positive children with SAM (HIV-SAM) and HIV-negative children with SAM. All participants with SAM are followed for 48 weeks post discharge, with longitudinal data collection and blood sampling. The study contains four nested substudies as shown in figure 1. A subgroup of children will be recruited to the enteropathy substudy for which they will have the same follow-up procedures but more intensive biological specimen collection including stool (all time points), urine after lactulose-mannitol (LM) challenge as an assessment of intestinal permeability and nasogastric aspirate (baseline only); these children are also included in microbiota and metabolomics substudies. Children with SAM for whom blood samples are available are included in the immunology substudy, for which circulating inflammatory mediators will be assayed; functional cellular immunology assays will be conducted for all children in the immunology substudy with sufficient sample volume (>2 mL) recruited after June 2017. A group of healthy children recruited from the same hospitals and communities, who are well-nourished and matched to children in the enteropathy substudy by age and HIV status, will have data and specimens collected to provide normative data for the laboratory substudies; these well-nourished controls will not be followed longitudinally.

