### Eligibility for enteropathy substudy

Children with SAM aged 6–59 months with a nasogastric tube in place (or due to be placed) are categorised into four groups (HIV-positive oedematous (group A -I); HIV-positive non-oedematous (group A-II); HIV-negative oedematous (group C-I) and HIV-negative non-oedematous (group C-II)) as shown in table 1. Children meeting eligibility criteria will be enrolled throughout the study recruitment period until sufficient specimens have been collected from the groups shown in table 1. Children in the enteropathy substudy are stratified into age bands (6–11 months, 12–23 months and 24–59 months) to enable age-matching of well-nourished controls. Children with underlying chronic gastrointestinal disease or a known malignancy are ineligible.

**Table 1 T1:** Enteropathy substudy groups

Children aged 6–59 months	SAM*		Well-nourished controls WHZ>–1
	Oedematous†	Non-oedematous	
HIV-positive (HIV PCR+ if <18 months; HIV antibody+ if >18 months)	n=50 (group A-I)	n=50 (group A-II)	n=100 (group B)
HIV-negative (HIV PCR– if<18 months; HIV antibody – if>18 months)	n=50 (group C-I)	n=50 (group C-II)	n=100 (group D)

Note that children below 6 months of age are excluded from the enteropathy substudy to avoid interrupting exclusive breast feeding during the lactulose-mannitol test.

*SAM defined according to WHO criteria.

†Presence of bilateral pitting pedal oedema.

SAM, severe acute malnutrition; WHZ, weight-for-height Z-score.

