### Baseline procedures

Baseline data on maternal and household characteristics, the child’s medical history and current illness are collected by a study nurse. Anthropometry, including body composition measured by whole-body (wrist-ankle) bio-electrical impedance analysis (BodyStat 1500MD; BodyStat, UK), leg length using an electronic knemometer (Zimbabwe only, due to availability of knemometers) and triceps, subscapular and supra-iliac skinfold thickness using callipers (Holtain, Crymych, UK), are undertaken at baseline. Blood (1 mL/kg up to 5.4 mL maximum) is collected at baseline into an endotoxin-free EDTA tube for all children and, in the enteropathy substudy, additionally into a PAXgene tube (PreAnalytiX, Hombrechtikon, Switzerland) for subsequent transcriptomic analysis. Blood is not collected from children with severe anaemia (known haemoglobin <60 g/L). HIV testing is carried out in accordance with national guidelines as part of routine clinical practice; where it has not been done, the child’s HIV status is ascertained using a rapid test antibody algorithm for children over 18 months, or HIV DNA PCR for children under 18 months. CD4 count/percentage and viral load are measured in HIV-positive children. Maternal HIV status is documented where available, so that HIV-exposed uninfected children can be identified. Blood samples are sent to research laboratories at each site to conduct whole blood stimulation and bacterial binding assays (as described in the immunology substudy) and to store aliquots of whole blood, peripheral blood cells and plasma at −80⁰C.^31^ In the enteropathy substudy, nasogastric aspirate, stool and urine (after an oral dose of lactulose and mannitol) are also collected. Lactulose and mannitol are ingested by the child after fasting and urine is collected over a 2-hour period to measure recovery of lactulose and mannitol, a measure of intestinal absorptive capacity and permeability, as previously described.^32^

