### Enteropathy substudy

The primary comparison for the enteropathy substudy will be between HIV-positive children with SAM (group A) and HIV-negative children with SAM (group C), stratified by presence or absence of oedema. Control groups (B and D) are well-nourished children with or without HIV, to provide normative data for biomarkers and to evaluate the impact of SAM within each HIV group. Thus, biomarkers among HIV-positive children with SAM will first be compared with HIV-negative children with SAM (to evaluate the impact of HIV) and, second, with well-nourished HIV-positive children (to evaluate the impact of SAM). Biomarkers among HIV-negative children with SAM will be compared with well-nourished HIV-negative children. For each continuous outcome, simple descriptive analysis will be used to compare groups during hospitalisation using t-tests on appropriately transformed data. For any outcome with moderate (p<0.05), evidence of difference between either group a regression model will be constructed including groups A, B, C and D to directly test (using interactions) whether there is a synergistic effect of HIV-SAM versus HIV-negative SAM versus HIV alone versus neither. These models will also be used to explore whether there is any evidence for heterogeneity in effects between oedematous and non-oedematous SAM. Associations between enrolment factors (eg, intestinal permeability and microbial translocation) will be explored using pairwise Spearman correlations and principal components analysis. Mean changes at the follow-up time points in each group will be estimated, and groups compared (as above) using generalised estimating equations. For outcomes that differ across SAM groups over time, multilevel models will be used to explore possible predictors from the other factors measured. Time to nutritional recovery will be compared using Kaplan-Meier and log-rank tests, and Cox models to adjust for baseline differences between groups.

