### Immunology substudy

Integrated profiles of innate immune cell function will be generated for each child using principal components analysis followed by hierarchical clustering.^65 66^ This data -reduction method identifies whether absolute levels of specific markers or relative differences between markers differentiate children into groups. The resulting innate immune profiles will be compared between HIV-SAM, HIV-negative children with SAM and well-nourished groups using univariable tests and multivariable analysis of variance of the principal components.

To address the relationship between immune function and infections, regression analyses will determine whether baseline innate immune profiles (or the individual parameters defining them) are associated with the infectious morbidity or mortality during hospitalisation, using logistic models for binary outcomes and linear models for duration. Key clinical characteristics, including age, sex, oedema and baseline WHZ, will be added to models to investigate their confounding effects. Multivariable stacked regression methods will be used to compare the impact of different factors on severe bacterial infections based on heterogeneity tests.

To determine whether treatment for SAM restores innate immune cell antibacterial function, mixed effects regression models will compare longitudinal changes in individual immune parameters, and the principal components calculated from the weights identified at baseline (which include well-nourished controls). Similarities and differences in longitudinal immune profiles will be compared between groups using non-metric multidimensional scaling.^65 67 68^ This approach will group children according to their composite innate immune function, allowing the duration and variability of immune restoration to be evaluated over the course of nutritional rehabilitation. Binary logistic regression will determine whether innate immune profiles at discharge are associated with morbidity or mortality during follow-up.

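### SAM versus well-nourished contrasts are planned without a site or calendar term, although control enrolment may run 12 months past SAM enrolment and controls are not matched on site; the exposure is mainly in the live immune assays

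*Protocol article*

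**What the plan says.** The relevant statements in the protocol article are these.

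- **Dates (Time frame and study status).** "Enrolment into the SAM cohorts began in July 2016 and ended in March 2018". Then: "Enrolment of well-nourished controls is expected to end in March 2019". No start date for control enrolment is given.
- **Matching (Study design; Well-nourished controls).** Controls are "matched to children in the enteropathy substudy by age and HIV status". They come from the same hospitals and communities as the cases, but no site proportions or calendar periods are set.
- **Live assays (Baseline procedures; Eligibility for immunology substudy).** "Blood samples are sent to research laboratories at each site to conduct whole blood stimulation and bacterial binding assays". Cellular assays apply to SAM children sampled after 1 June 2017.
- **Stored material.** The footnotes to table 2 say that culture supernatants and cells are stored after stimulation. The enteropathy, microbiota and metabolomics substudies work from stored samples.
- **Enteropathy analysis.** "simple descriptive analysis will be used to compare groups during hospitalisation using t-tests on appropriately transformed data". A regression on groups A to D, with interactions and an exploration of oedema, follows only for outcomes with p<0.05. It names no site or date term.
- **Immunology analysis.** "The resulting innate immune profiles will be compared between HIV-SAM, HIV-negative children with SAM and well-nourished groups using univariable tests", together with a multivariable analysis of variance of the principal components. Age, sex, oedema and WHZ are named only for the models of infectious morbidity and mortality.

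**The concern.** A control sampled between April 2018 and March 2019 has no SAM baseline sample from the same period. If the controls also come from the three hospitals in different proportions from the cases, SAM status is partly aligned with laboratory and with calendar time. An unadjusted comparison then attributes any difference between laboratories, or any change in reagents or operators over time, to SAM.

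This matters most where the laboratory step is done once on fresh blood and cannot be repeated. Stimulation and bacterial binding are such steps. What is at stake is the claim that innate immune function is compromised in SAM. The yardstick for recovery is also affected, because the longitudinal principal components use baseline weights that include the controls.

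**Working it through.** **1. The plan's own power figure.** Enteropathy sample size: 100 v 100, two-sided alpha 0.025, LM difference 0.16, SD 0.36. The standardised difference is 0.16/0.36 = 0.444. Dividing by √(2/100) = 0.1414 gives 3.143, and 3.143 − 2.241 = 0.901, so power is 81.6% by the normal approximation (81.1% by noncentral t). The stated figure of more than 80% reproduces, and nothing below changes it.

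**2. Calendar windows, counted inclusively.**
- SAM enrolment, July 2016 to March 2018: 21 months.
- SAM baselines with live assays, June 2017 to March 2018: 10 months.
- Controls only, April 2018 to March 2019: 12 months.

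**3. Share f of controls without a concurrent SAM baseline.** The start of control enrolment is not given, so f could lie anywhere from near 0 to 100%. Two scenarios with even accrual (an assumption):
- controls from July 2016: 12/33 = 36%;
- controls with live assays from June 2017: 12/22 = 55%.

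Only the second matches the live-assay period.

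**4. Shift of the contrast.** Shift = f × d, where d is the drift between periods in SD units. The protocol gives no value for d; 0.25 and 0.5 are assumed.

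| f | d = 0.25 | d = 0.5 |
|---|---|---|
| 12/33 | 0.09 SD | 0.18 SD |
| 12/22 | 0.14 SD | 0.27 SD |

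(Rounding the share to 0.55 first gives 0.28 in the last cell.)

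**5. What such a shift does to the test if SAM has no true effect.** Rejection rate = 1 − Φ(c − shift/SE) + Φ(−c − shift/SE), where c is the two-sided critical value.
- Immunology, 200 v 200, alpha 0.05, SE = √(2/200) = 0.10, f = 12/22: 28% at d = 0.25 and 78% at d = 0.5, against a nominal 5%.
- Enteropathy, 100 v 100, alpha 0.025, SE = 0.1414, f = 12/33: 4.5% at d = 0.2 and 17% at d = 0.5, against a nominal 2.5%.

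**6. Site mix.** For 100 v 100 at alpha 0.025, assume a 20-point imbalance in site share and a 0.5 SD difference between sites. The shift is 0.2 × 0.5 = 0.10 SD and the rejection rate is 6.4%.

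**7. Cost of using concurrent controls only.** With f = 12/22, 200 × 10/22 = 91 controls remain. SE = √(1/200 + 1/90.9) = 0.1265 against 0.10, about 26% larger.

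**The case against.** The strongest replies, and what stands of each:

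- **A covariate list belongs in an analysis plan or laboratory procedure, and the article calls all analyses exploratory.** This limits the weight of the point. It does not remove it, because the article names the tests, and those tests have no site or date term. Unadjusted p-values are still to be read as strength of evidence, and exploratory status does not reduce bias.
- **Controls come from the same hospitals and communities.** This reduces site confounding but fixes no proportions.
- **Most material can be batched.** This stands. Stool, urine and plasma are stored, as are culture supernatants and cells. Only the stimulation and binding steps cannot be rerun in common batches, so a reader should not infer an equal threat of assay drift to the microbiota, metabolomics or enteric markers. For LM ratio, the cited means of 0.42 and 1.3 with SD 0.36 differ by 0.88/0.36 = 2.4 SD, which a shift of 0.09 to 0.27 SD would neither create nor reverse.
- **Season.** A reader might infer seasonal confounding. The dates do not support it, because the extension adds one full year. With even accrual, April to May makes up 0 of 10 SAM months and 2 of 22 control months (9%) for live assays. From July 2016, April to June makes up 3 of 21 (14%) and 6 of 33 (18%).
- **HIV-positive versus HIV-negative SAM (A v C).** A reader might extend the point to this contrast. Both groups closed by March 2018, so the control lag does not touch it. Enrolment "until sufficient specimens have been collected from the groups shown in table 1" could close the groups at different dates. A figure for lost power would, however, need the 40% inpatient HIV prevalence to hold among children with nasogastric tubes in each oedema group, and would need an assumed sign of drift. The document supports neither.

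**Conclusion.** The point holds in limited form. The documents establish the lag of up to 12 months, matching without site or calendar time, live assay steps in separate site laboratories, and stated comparisons with no site or date term. Together these allow laboratory or calendar differences to be read as an effect of SAM, chiefly in the immunology SAM versus well-nourished contrast.

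The size is not known. The range of 0.09 to 0.27 SD, and the rejection rates that follow from it, rest on even control accrual and an assumed drift of 0.25 to 0.5 SD. They show what could happen and do not estimate what did. If most controls were enrolled before April 2018 the calendar component is small, and site mix is the remaining issue. No stated sample size or power figure is wrong on this account.

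**What to change.** 1. In the enteropathy and immunology analysis sections, estimate the same SAM versus well-nourished contrasts with linear models that include study site and age band (the matching factor), in place of the unadjusted t-tests, univariable tests and multivariable analysis of variance. This costs a few degrees of freedom and uses data already recorded.
2. For the live stimulation and binding assays, add a sensitivity analysis that either adjusts for calendar period or restricts to controls sampled while SAM children were being enrolled at the same site. The price is precision: a standard error about 26% larger if 55% of controls are non-concurrent. This is why calendar period fits better in a sensitivity analysis than in the main model.
3. Assay stored case and control samples together in randomised batches.
4. Report control enrolment dates by site, so that the non-concurrent share is known rather than assumed.

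Using SAM follow-up samples from the control-only period to estimate and remove drift need not be required, since drift would first have to be separated from recovery and survivor selection.

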## Discussion

HOPE-SAM aims to document the short- and long-term clinical and nutritional outcomes of HIV-positive and HIV-negative children with SAM, and to identify the factors at presentation and at discharge from hospital that independently predict these outcomes. Mechanistic substudies aim to evaluate the contribution of enteropathy, microbiota, metabolome and innate immune cell function to these clinical outcomes. The prevalence of malnutrition in HIV-positive children is as high as 40% in some settings and the challenges of managing this population are well recognised.^69^ The WHO protocol on management of SAM aims to reduce case fatality below 10%, but rates as high as 35% are still reported among HIV-positive children.^5 70^ No studies have systematically and longitudinally collected morbidity data in HIV-SAM, or documented repeat hospitalisations and mortality after discharge from hospital, particularly in the current era where ART is available on diagnosis. HOPE-SAM will provide a unique opportunity to enrol and follow a cohort of children managed for SAM in three large hospitals across two sub-Saharan African countries at several time points over a 1-year period. Nested longitudinal laboratory substudies aim to better characterise the pathogenesis of SAM in HIV-positive and HIV-negative children, to determine whether pathogenic processes are normalised during nutritional rehabilitation and follow-up, and to identify potential mechanistic pathways. Our ultimate goal is to use the findings generated in this study to inform new intervention approaches that can be evaluated in clinical trials to improve outcomes among children with SAM.
